### Follow-up

Subjects in all four arms of the study will be followed up, three times in 12 months following recruitment. Blood pressure measurement for treatment outcome will be done. The Self-efficacy for Appropriate Medication Adherence Scale (SEAMS) is an adherence-monitoring scale that will be used to collect information from participants regarding their adherence to medication self-reporting. Apart from SEAMS, self-reporting pill counting for measuring medication adherence will be used, and health-related quality of life using EuroQol 5-Dimension-3-level (EQ-5D-3L) and a visual analog scale (EQ-VAS) will also be assessed. All the above assessments will be done at baseline, 6 months, and 12 months of follow-up.

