We will assess self-reported information regarding the number of tablets that will be utilized by participants within the specified timeline divided by the number of pills prescribed for that time multiplied by a hundred for the last 7 days. A rate of ≥ 80% will be considered adherent and vice versa [7, 8]; thereby, the percentage of participants who are successful in achieving adherent status between baseline and 12 months will be evaluated. In addition, to measure the adherence score at baseline, 6 months, and 12 months post-intervention, an Urdu/English version of the “Self-efficacy for Appropriate Medication Adherence Scale” (SEAMS) will be employed [33, 34]. The SEAMS is a 13-item measure for evaluating medication self-efficacy in chronic disease management that looks to be appropriate for people with low literacy abilities [34]. This survey will use a three-point response system, with 1 indicating lack of confidence, 2 indicating moderate confidence, and 3 indicating extreme confidence. The 13-item scale had a range of possible scores from 13 to 39. High scores indicate better adherence.

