Each of the participants will be given a paper-based questionnaire. Interviewers will read the questions to the participants and note down their answers if they have difficulty filling out the response. The paper-based questionnaires “Self-efficacy for Appropriate Medication Adherence Scale” (SEAMS) [34] contain socio-demographic, health-related, and adherence-related validated questions that would be employed in Urdu and English. The SEAMS is a 13-item measure for evaluating medication self-efficacy in chronic disease management that looks to be appropriate for people with low literacy abilities [34]. This survey used a three-point response system, with 1 indicating lack of confidence, 2 indicating moderate confidence, and 3 indicating extreme confidence. The 13-item scale had a range of possible scores from 13 to 39. In terms of drug adherence, greater ratings indicated higher levels of self-efficacy and vice versa. It is a dependable and precise device. Principal component factor analysis was used to determine the study’s validity. The researchers established a two-factor solution that accounted for 52.3% of the variance. Test-retest reliability had a moderate level of dependability (Spearman’s *r* = 0.62, *p* = 0.001). Internal consistency (Cronbach’s alpha = 0.89) is good [34].

The participants will be asked how many tablets they were prescribed for the period in question, as well as how many pills they took and missed during that time. Adherence rates will be calculated by dividing the number of pills ingested during a period by the number of tablets suggested for that period. Based on past research, an 80% cut-off value has been developed. Non-adherents will account for less than 80% of the rate, while adherents will account for more than 80% [7].

At the end of the sixth and twelfth months, participants who completed the baseline survey in all four groups will be invited to one of the study institutes to be questioned by qualified interviewers or over the phone who will be unable to come to complete the second round of blood pressure measurement, SEAMS filling, health-related quality of life post-intervention using EQ-5D-3L and EQ-VAS, and pill-counting information (Table 2).

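### SEAMS is a self-efficacy scale by the protocol's own description, but it is labelled and interpreted as an adherence score, so a gain in confidence could be reported as better adherence

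*Protocol article*

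**What the plan says.** Outcome measures introduces the scale with "The SEAMS is a 13-item measure for evaluating medication self-efficacy in chronic disease management" and gives the response options as "with 1 indicating lack of confidence, 2 indicating moderate confidence, and 3 indicating extreme confidence". The same paragraph says that SEAMS will be used "to measure the adherence score at baseline, 6 months, and 12 months post-intervention" and closes with the rule "High scores indicate better adherence".

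Follow-up says that SEAMS "is an adherence-monitoring scale that will be used to collect information from participants regarding their adherence". Statistical analysis lists SEAMS beside pill counting under the heading of adherence in its subgroup sentence. Data management describes the same scale and score range but says that "greater ratings indicated higher levels of self-efficacy and vice versa".

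Tablet-taking has its own measure: self-reported tablets taken over tablets prescribed in the last 7 days, as a percentage, with 80% as the cut-off for being adherent. The Abstract names change in medication adherence as a secondary outcome, and the third research objective asks for mean differences in adherence among the four groups at 0, 6 and 12 months. Self-efficacy is not named as an outcome in its own right.

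**The concern.** Confidence in taking medicines and actually taking them are different things. An intervention can move the first without the second, and these modules are built to work on beliefs: the Background states the aim of altering beliefs about adherence, Table 1 lists changing beliefs and encouragement as counselling content, and the section on educational support with peer counseling addresses attitudes to drug-taking. A between-group difference in SEAMS is therefore plausible even if tablets taken do not change. Under the stated rule, that difference would be written up as improved adherence, on a named secondary outcome and one of four objectives.

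**Working it through.** This is a question of construct, so the check is mainly a comparison of the protocol with itself.

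**1. What the scale measures.** There are 13 items, each rated 1 to 3 for confidence. The lowest total is 13 × 1 = 13 and the highest is 13 × 3 = 39, which agrees with "The 13-item scale had a range of possible scores from 13 to 39". The total is thus a sum of confidence ratings. The items are not shown, so this rests on the scale's name, its description and its response options.

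**2. How each section reads it.**

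| Section | Reading of SEAMS |
|---|---|
| Study design | listed apart from the number of tablets taken; not called adherence |
| Follow-up | adherence-monitoring scale |
| Outcome measures | self-efficacy by description; adherence by use and by interpretation rule |
| Statistical analysis (subgroups) | adherence, beside pill counting |
| Data management | self-efficacy |

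**3. Which reading fits the protocol's definition.** The Background defines adherence by how far patients keep to the drug schedule prescribed for them, which is a behaviour. The 7-day tablet percentage fits that definition. A confidence total does not.

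**4. Whether the protocol links the two.** The validation evidence in Data management is a two-factor solution explaining 52.3% of variance, a test-retest correlation of 0.62 and a Cronbach's alpha of 0.89. These concern structure and reliability. None relates SEAMS to tablet-taking.

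**5. Which measure answers the third objective.** The objective asks for mean differences. Statistical analysis offers ANOVA-type or rank tests for the adherence difference without saying which variable they use. It then takes pill counting in a separate sentence, with dichotomous adherence, frequencies and a chi-square test. Outcome measures attaches the term adherence score to SEAMS only. Together, these make SEAMS the variable for the mean comparison, while the pill measure yields proportions.

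**6. What is not affected.** The sample size rests on systolic blood pressure: SD 18.5, difference 148 − 143 = 5, two-sided 5%, power 90%.

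- n per group = 2 × 18.5² × (1.960 + 1.282)² / 5² ≈ 287.7, rounded up to 288
- with 30% attrition, 288 / 0.70 = 411.4, rounded up to 412
- total = 4 × 412 = 1648, as stated

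SEAMS does not enter this calculation.

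**The case against.** The strongest reply is that the protocol already separates the two measures. Outcome measures gives the tablet percentage first and brings in SEAMS as an addition, Follow-up names pill counting for adherence apart from SEAMS, and pill data have their own test. A rise in SEAMS with no change in tablets would be visible, and any reader of the report would see the scale's name. This stands, and it limits the harm. It does not remove the stated interpretation rule or give the pill percentage a comparison of its own.

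Several stronger readings are tempting, and the protocol does not support them:

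- **That two sections state flatly opposed rules.** Outcome measures itself calls SEAMS a self-efficacy measure just before its adherence rule, and the self-efficacy sentence in Data management opens with a reference to drug adherence. The usage is inconsistent, but the two rules are not cleanly opposed.
- **That the Abstract assigns SEAMS to the adherence tests.** It speaks only of adherence scores and never names the scale. The link is an inference through Outcome measures.
- **That SEAMS is a poor indicator of adherence.** The cited validation sources are not at hand and the protocol gives no correlation with tablet-taking, so the strength of the relation is unknown in either direction.
- **That the pill measure must be the only adherence outcome.** That is partly a preference. The pill measure is also a self-report, covers 7 days, and is open to recall and desirability error. Ethical considerations itself expects embarrassment over poor adherence.

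**Conclusion.** The point holds as a fault of labelling and interpretation with a consequence for one secondary outcome. As written, a between-group gain in confidence may be reported as a gain in adherence, and the mean comparison serving the third objective in effect rests on SEAMS. The second part assumes that the adherence score in the analysis is the one so named in Outcome measures. If the ANOVA-type tests were also meant for the pill percentage, the protocol does not say so.

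No numerical bias can be attached to this. The change is worth making because it alters what the trial may conclude about adherence.

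**What to change.** 1. In Follow-up, Outcome measures and Statistical analysis, name SEAMS as a separate secondary outcome, medication self-efficacy.
2. In Outcome measures, replace the closing interpretation rule with the self-efficacy reading given in Data management.
3. State that conclusions about adherence rest on the 7-day self-reported pill measure.
4. In Statistical analysis, add a between-group comparison of the pill percentage at 0, 6 and 12 months, alongside the 80% classification, so that the third objective is answered on the scale it asks for.

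Both measures are already collected at all three visits, so no new data are needed. The cost is more than relabelling, since item 4 is a small re-specification of the analysis and should be settled before the 12-month analysis. The weaknesses of a 7-day self-report should be stated as a limitation of any adherence claim.

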### Statistical analysis

The intention-to-treat analytic method will be conducted [35, 36]. Mixed-effects modeling with repeated measures will be employed for the primary outcome change in systolic blood pressure at 0, 6, and 12 months. To estimate treatment effects at each time point, an interaction between time and the groups will be fitted. For the primary and secondary outcomes measuring systolic blood pressure and medication adherence difference between and with the group at 0, 6, and 12 months, parametric (ANOVA/repeated measure ANOVA) and non-parametric tests *(*Kruskal*-*Wallis test*/*Friedman test/Wilcoxon signed*-*rank test) will be used. We shall account for the multiple time points statistically by using Tukey’s exact test. The Tukey test will be utilized for multiple comparisons and adjustment for multiple comparisons will be performed by Bonferroni correction. All the outcomes will be analyzed at 0, 6, and 12 months; however, the final analysis will be at 12 months from baseline. The *p*-value for the significance test will be set at *p* < 0.05. Pill counting data, adherence assessment at dichotomous variables, frequencies, and the chi-square test will all be used. By using the general estimating equation (GEE) with negative binomial regression, at 12 months post-follow-up, the covariates affecting primary and secondary outcomes including, age, gender, ethnicity, living status, education, monthly income, use of reminder, health insurance coverage, body mass index (BMI), diabetes, duration of illness, number of comorbid conditions, number of daily medication use, dose frequency will be determined and controlled. A complete analysis plan will be established for data analysis, including subgroup analyses and sensitivity analyses.

Sub-group analyses of the change in systolic blood pressure, the adherence to medication over the previous 12 months will be conducted by age (21–29 years, 30–49 years, 50 years and above), sex (male, female), adherence (SEAMS, pill-counting), and health-related quality of life (using EQ-5D-3L and EQ-VAS). Missing data from attrition will be handled using a multiple imputations approach at 12 months.

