### Sample size

For comparing different interventions among the four groups, the sample size is computed through the STATA software using a standard deviation of 18.5 in systolic blood pressure taken from a Pakistani study [9], population means of 148 and 143 respectively, as 5 mmHg reduction in systolic blood pressure is related to clinical importance regarding decreasing the risk of coronary artery disease [25]. A two-sided level of significance of 5% and a power of 90% with a 30% attrition rate between the baseline and 12 months of the intervention period were used. The total sample size calculated is 1648 with 412 in each group.

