### Randomization and blinding

To avoid any potential bias, a simple complete randomization procedure will be utilized [26]. A computer-generated, simple complete random approach will be used to divide participants into four groups [27]. To keep their identities hidden, all participants will be assigned an identification number. To keep the allocation of participants into four groups hidden from the research staff, tight concealment of allocation will be observed. Before allotment, written assignments will be sealed in opaque packets with tagged identifying numbers [28].

All subsequent randomization processes will be completed by an independent biostatistician who will no longer be a participant in the trial. Independent personnel will be involved in the randomization, evaluation, and intervention delivery. The staff involved in data collection and outcome assessment will be blinded. They will be unaware of the allocation of any group [29].

The recruitment process will continue until a final sample size of 1648 people from four teaching hospitals is reached. Participants’ follow-up period is 12 months from the point of randomization (Fig. 2).

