	**mHealth intervention**	

The first group will receive no intervention and only standard hospital care (as per the practice of the hospital); the second group will receive monthly Ed-counselling sessions in addition to standard care; the third group will receive daily written and voice reminders and once weekly an education-led video in addition to standard care; the fourth group will receive Ed-counselling sessions every month, daily written and voice reminders, and once weekly an education-led video in addition to standard care.

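### Month-0 systolic blood pressure is modelled as an outcome and baseline adjustment is not stated, so the 12-month effect is less precise than the collected data allow, and the planned power depends on which effect is primary

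*Protocol article*

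**What the plan says.** All places are in the protocol article.

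- **Statistical analysis:** "Mixed-effects modeling with repeated measures will be employed for the primary outcome change in systolic blood pressure at 0, 6, and 12 months". A time-by-group interaction is to give treatment effects at each time point. The final analysis is at 12 months.
- **Outcome measures:** the primary outcome is likewise the change in systolic blood pressure (SBP) at 0, 6 and 12 months.
- **Covariates:** a separate generalised estimating equation (GEE) with negative binomial regression at 12 months carries fourteen named covariates, beginning "age, gender, ethnicity, living status, education, monthly income, use of reminder, health insurance coverage, body mass index (BMI), diabetes". Baseline SBP is not among them.
- **Research objectives:** these speak of mean differences in SBP among the four groups at 0, 6 and 12 months, which describes levels.
- **Sample size:** this also works with levels: "standard deviation of 18.5 in systolic blood pressure taken from a Pakistani study" and "population means of 148 and 143 respectively, as 5 mmHg reduction in systolic blood pressure is related to clinical importance". The error rates and dropout are "A two-sided level of significance of 5% and a power of 90% with a 30% attrition rate". Neither an SD of change nor a correlation between visits is given.

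**The concern.** Change at month 0 is zero for everyone, so it cannot be an outcome. If SBP at the three visits is modelled instead, a month-0 group contrast measures only chance imbalance, because baseline precedes treatment.

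The more useful role for the baseline value is as a predictor of the 12-month value. With the baseline on the outcome side and the group means free to differ there, part of its information about the 12-month effect is lost.

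The text also leaves open whether the primary effect is the difference in change or the difference in level at 12 months. These have different standard errors, and the sample size was computed for only one of them.

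**Working it through.** **Inputs.** From the Sample size section: SD 18.5, difference 148 − 143 = 5 mmHg, two-sided alpha 0.05, power 90%, attrition 30%, 412 per group. The correlation rho between baseline and 12-month SBP is not given, so a range is shown. Assumptions: equal SD at both times and, for the mixed model, dropout at random. The mixed-model figures use months 0 and 12 only.

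**Reproducing the plan.** n = 2 × (1.96 + 1.2816)² × 18.5² / 5² = 287.7, so 288 per arm. 288 / 0.70 = 411.4, so 412. 4 × 412 = 1648, as stated. This is a pairwise comparison of levels with no baseline term.

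**Power.** Power = Φ(5/SE − 1.96), with SE = 18.5 × √(2v). The value of v depends on the analysis:

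- A. Difference in change, complete cases: v = 2(1 − rho)/288
- B. Difference in change, unconstrained mixed model with all 412 baselines: v = (1 − rho²)/288 + (1 − rho)²/412
- C. 12-month level, complete cases, unadjusted: v = 1/288
- D. 12-month level, same mixed model as B: v = (1 − rho²)/288 + rho²/412
- E. 12-month difference, baseline-adjusted: v = (1 − rho²)/288

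| rho | A | B | C | D | E |
|---|---|---|---|---|---|
| 0.3 | 78.3% | 82.6% | 90.0% | 90.8% | 92.5% |
| 0.4 | 84.2% | 87.4% | 90.0% | 91.4% | 94.3% |
| 0.5 | 90.0% | 92.1% | 90.0% | 92.1% | 96.3% |
| 0.6 | 95.2% | 96.2% | 90.0% | 93.0% | 98.2% |
| 0.7 | 98.7% | 99.0% | 90.0% | 94.0% | 99.5% |

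Worked line for rho 0.3:
- A: SD of change = 18.5 × √1.4 = 21.9; SE = 21.9 × √(2/288) = 1.82; Φ(2.74 − 1.96) = 78.3%.
- E: SD = 18.5 × √0.91 = 17.65; SE = 1.47; Φ(3.40 − 1.96) = 92.5%.

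**Thresholds for 90%.**
- A equals C when 2(1 − rho) = 1, so rho = 0.5.
- B equals C when (1 − rho)²/412 = rho²/288, so (1 − rho)/rho = √(412/288) = 1.196 and rho = 0.455.
- C, D and E have no threshold. E equals 90.0% at rho 0 and rises from there.

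**Precision.** E has the smallest v in every row. At rho 0.5 its variance is 1 − 0.25 = 0.75 of that of A, equivalent to 288/0.75 = 384 completers per arm. Against B or D at rho 0.5 the ratio is 0.002604/0.003211 = 0.81.

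A simulation of 4,000 two-arm trials with 288 per arm agreed with the complete-case formulas. At rho 0.5 the standard errors were 1.55 (A), 1.54 (C) and 1.34 (E), against 1.54, 1.54 and 1.33.

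**The case against.** A repeated-measures model of SBP at three visits with a time-by-group interaction is a recognised analysis, and the month-0 contrast is a by-product of it. The article makes 12 months the final analysis. It also promises a complete analysis plan, and its covariate list is open-ended and belongs to the GEE. Silence about covariates in the primary model would therefore be no finding by itself. All this is fair. What remains is what the article does fix: it puts month 0 on the outcome side and calls the outcome a change, while powering the trial on levels.

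Four stronger readings are tempting, but the document does not support them.

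- **That the stated power holds only if rho is at least 0.5.** This is exact only for a complete-case difference in change. The threshold is about 0.46 in the mixed model, and there is none for the 12-month level difference, which the Research objectives and Sample size sections describe.
- **That power is lost and chance baseline differences also remain in full.** These belong to different readings. A change score subtracts the baseline, and the unadjusted level comparison keeps its 90%.
- **That omitting hospital is a flaw of the same kind.** The control group receives "only standard hospital care (as per the practice of the hospital"), but no difference between hospitals is reported. Since "a simple complete randomization procedure will be utilized", there is no stratification factor to carry into the model. Validity is not threatened, and no between-hospital variance is given from which to size a gain.
- **That the Bonferroni correction belongs in this calculation.** The number of comparisons is not stated, and its absence from the sample size is a separate issue.

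**Conclusion.** The point holds as one of efficiency and clarity, not bias. On either reading of the primary effect, the analysis as written is less precise than a baseline-adjusted one, for any rho strictly between 0 and 1.

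The size depends on rho, which must be assumed. If the effect is the difference in change, power falls below 90% once rho is under about 0.5 (complete cases) or 0.46 (mixed model). If it is the 12-month level difference, the planned power is met at any rho, and the loss is only the gap between columns D and E.

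The baseline-adjusted analysis reaches at least 90% at every rho, so it also removes the mismatch between the outcome definition and the sample size. All figures are for a single comparison at the 5% level with 288 completers per arm.

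**What to change.** Name one primary estimate: the 12-month between-group difference in SBP from the mixed model. Take SBP at 6 and 12 months as the outcome and baseline SBP, interacted with time, as the covariate. An equivalent choice keeps month 0 in the model but constrains the baseline means to be equal across arms. Drop the month-0 treatment contrast and use the same definition under Outcome measures.

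Hospital may be added as an optional fixed effect for possible precision.

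The cost is wording only. Baseline SBP is already measured, and 412 per group remains sufficient for a single 5% comparison under the stated assumptions.

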**Methods:**

We chose a double-blinded pragmatic randomized-controlled with factorial design for this investigation. The trial is going to recruit 1648 hypertensive patients with coronary artery disease at the age of 21 to 70 years. All participants will already be on anti-hypertensive medication and own a smartphone. They will be randomized into four groups with each having 412 participants. The first group will only receive standard care; while the second group, in addition to standard care, will receive monthly Ed-counselling (educational booklets with animated infographics and peer counseling); the third group will receive daily written and voice reminders and an education-led video once weekly together with standard care; while the fourth one gets both interventions given to second and third groups respectively. All groups will be followed-up for 1 year (0, 6, and 12 months). The primary outcome will be the change in systolic blood pressure while secondary outcomes include health-related quality of life and changes in medication adherence. For measuring changes in systolic blood pressure (SBP) and adherence scores difference at 0, 6, and 12 months between and within the group, parametric (ANOVA/repeated measure ANOVA) and non-parametric tests *(*Kruskal*-*Wallis test*/*Friedman test*)* will be used. By using the general estimating equation (GEE) with negative binomial regression, at 12 months, the covariates affecting primary and secondary outcomes will be determined and controlled. The analysis will be intention-to-treat. All the outcomes will be analyzed at 0, 6, and 12 months; however, the final analysis will be at 12 months from baseline.

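### The primary outcome, change in systolic blood pressure, is given a mixed model, ANOVA, rank tests and a GEE, and the protocol does not say which one decides the trial

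*Protocol article*

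**What the plan says.** The Statistical analysis section opens its treatment of the primary outcome with one model: "Mixed-effects modeling with repeated measures will be employed for the primary outcome change in systolic blood pressure at 0, 6, and 12 months". It adds that treatment effects at each visit will come from a time-by-group interaction.

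The next sentence assigns further methods to the same outcome: "For the primary and secondary outcomes measuring systolic blood pressure and medication adherence difference between and with the group" will be examined with ANOVA or repeated-measures ANOVA and with Kruskal-Wallis, Friedman and Wilcoxon signed-rank tests. The parametric and rank families are joined by the word and; no condition chooses between them. Later in the section, a GEE with negative binomial regression is applied at 12 months to covariates affecting primary and secondary outcomes. Significance is set at p < 0.05. Twelve months is fixed as the final time point, but no test is fixed with it.

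The Abstract (Methods) describes the SBP analysis differently. "For measuring changes in systolic blood pressure (SBP) and adherence scores difference at 0, 6, and 12 months between and within the group" it lists ANOVA, repeated-measures ANOVA, Kruskal-Wallis and Friedman, then the GEE. The mixed model does not appear.

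On missing data the Statistical analysis section says: "Missing data from attrition will be handled using a multiple imputations approach at 12 months". It does not mention a missed 6-month visit, and it does not say which of the analyses use the imputed data.

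**The concern.** A superiority trial needs one pre-specified test of its primary hypothesis. Here at least four families of method are attached to SBP change with equal standing, and a reader of the Abstract would name a different primary analysis from a reader of the Methods. This is a conflict between published statements, not a detail left to a later analysis plan.

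The 5% error rate is at stake. Each method alone holds its level, but they are imperfectly correlated, so the chance that at least one is significant under the null exceeds 5%. The Tukey and Bonferroni provisions in the same section address time points and multiple comparisons. They do not address a choice among methods for the same hypothesis.

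The methods also answer different questions. Friedman and Wilcoxon signed-rank, applied across visits, compare times within an arm. A negative binomial model is for counts and does not suit a continuous change that can be negative.

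**Working it through.** **1. The plan's own sample size.** Inputs from the Sample size section: "using a standard deviation of 18.5 in systolic blood pressure"; "population means of 148 and 143 respectively", so a difference of 5 mmHg; and "A two-sided level of significance of 5% and a power of 90% with a 30% attrition rate".

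- Per group: n = 2 × (z₀.₉₇₅ + z₀.₉₀)² × SD² / difference² = 2 × (1.960 + 1.282)² × 18.5² / 5² ≈ 287.7, rounded up to 288.
- With attrition: 288 / 0.70 = 411.4, rounded up to 412.
- Total: 4 × 412 = 1648.

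This matches the stated figure exactly. It is a two-group comparison of means, so the calculation itself does not show which listed method was meant to be primary.

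**2. Error rate if the choice of test stays open.** Null trials were simulated with four groups of 288, normally distributed SBP, SD 18.5, and visits at 0, 6 and 12 months. The within-patient correlation was assumed equal between visits, at 0.3, 0.5 or 0.7, with 4000 trials for each value. Each test alone rejected in about 5% of trials. The chance that at least one is below 0.05:

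| Candidate tests | Chance of at least one p < 0.05 |
|---|---|
| ANOVA and Kruskal-Wallis on 12-month change | about 6% |
| Those two plus the repeated-measures ANOVA group-by-time interaction | about 8–10% |
| ANOVA and Kruskal-Wallis on the 12-month value, plus the same interaction | about 10–11% |
| All five of the above | about 13–14% |

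The Monte Carlo standard error near 10% is √(0.10 × 0.90 / 4000) ≈ 0.5 percentage points, so differences of one point between runs are noise. Adding a baseline-adjusted 12-month test as a sixth candidate gave 13.8–14.1%.

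The negative binomial GEE was not simulated, and the mixed model was not fitted as such. The table therefore illustrates the size of the problem and does not cover every listed method.

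**3. Missed 6-month visits.** Classical repeated-measures ANOVA and Friedman need all three visits. If imputation fills month 12 only, a person without a 6-month value is still excluded from both. The document gives no rate for this. The calculation below assumes analysis of observed data at the planned attrition (412 × 0.70 = 288.4 per group), with a further share of 12-month completers having missed month 6:

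| Assumed share missing month 6 | Per group with all visits | Two-group power for 5 mmHg |
|---|---|---|
| 0% | 288 | 90.0% |
| 5% | 273 | 88.4% |
| 10% | 259 | 86.8% |
| 20% | 230 | 82.6% |

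The power column uses the plan's own two-group calculation, not the power of a repeated-measures ANOVA.

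**The case against.** The best defence is that the mixed model already is the primary analysis. It comes first, it is the only method given to the primary outcome alone, and it has a stated treatment term. The section also promises a complete analysis plan. This makes the mixed model the natural choice for the fix. It does not settle the text, because the later sentence names the primary outcome again and the Abstract leaves the mixed model out.

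It is also fair that the inflation is conditional. No sentence says that whichever test succeeds will be reported, and the figure depends on the candidate set. The five-test figure includes a separate choice, between the 12-month value and the change from baseline. Both limits stand, which is why the result is given as a range.

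Three stronger readings are tempting, and the document does not support them.

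- **Large loss of participants, contradicting intention-to-treat.** One might take 0.30 × 1648 ≈ 494 people as excluded from complete-visit tests. That ignores the multiple imputation planned for attrition. The 12-month wording may even describe when imputation is done and not which visit it covers. What remains is the possible gap at month 6.
- **A diluted effect.** A repeated-measures ANOVA group main effect averages over month 0, so 5 mmHg present at both later visits would appear as 5 × 2/3 ≈ 3.3 mmHg. The protocol never names that main effect as its treatment test; the only estimation rule it states is the interaction.
- **Friedman and Wilcoxon as faulty treatment tests.** The Abstract states a within-group purpose as well as a between-group one, and these tests can serve it. They need a label that keeps them to that role.

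**Conclusion.** The point holds as a conflict of specification. Several analyses are assigned to one primary outcome without ranking, and the Abstract and the Methods disagree on what they are. If any of them could be reported as the primary result, the 5% error rises to about 6–11% with two or three candidates and about 13–14% with five. Those figures rest on 288 per group, normal data, an assumed correlation of 0.3–0.7 and the candidate sets shown. Within that range the correlation matters little; the number and kind of candidates matter more.

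The month-6 imputation gap is a secondary point of unknown size. The sample size is reproduced and is not in question. This should be corrected, but it does not show that the design fails or that intention-to-treat is breached.

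**What to change.** - Name the mixed model's 12-month group contrasts, in all randomised participants with available data, as the single primary analysis of SBP.
- Label ANOVA, the rank tests and the GEE as supportive or sensitivity analyses. State that Friedman and Wilcoxon signed-rank are within-arm description only and are not evidence of a treatment effect. Including the GEE in this step matters, because otherwise a competing model for the primary outcome remains.
- Bring the Abstract into line with the Statistical analysis section.
- State that multiple imputation covers missing values at both 6 and 12 months, and which analyses use the imputed data.

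The cost is wording only. There is no new data collection, 1648 stays as it is, and naming one test keeps the primary hypothesis from being judged by whichever method happens to succeed.
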